#### Secondary outcomes - resilience

Assuming resilience scores are not normally distributed (as with the data from the pilot study) comparison of median scores will be made post-test between Grade 10 students in intervention and control schools to determine intervention effectiveness. Linear regression models (GEE) will test differences in overall sub-scale levels of resilience factors (predictor variable being treatment group).

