#### Secondary outcome measures - resilience

Items from the California Healthy Kids Survey will be used to measure student internal and external resilience. The survey addresses six internal resilience factor subscales and eight external resilience factor subscales which have demonstrated adequate reliability [31]. The internal resilience subscales include Likert scale items addressing: cooperation and communication (2 items); self-efficacy (4 items); empathy (3 items); problem solving (3 items); self-awareness (3 items); goals and aspirations (3 items); school support (6 items); school meaningful participation (3 items); community support (6 items); community meaningful participation (3 items); home support (6 items); home meaningful participation (3 items); peer caring relationships (3 items); pro-social peers (3 items).

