#### Primary outcomes – substance use

Comparisons in prevalence of substance use will be made between Grade 10 students in intervention and control schools at follow up to determine intervention effectiveness for each outcome measure. Generalized linear models (generalized estimating equation (GEE approach)) will be used [58]. The GEE will cater for dichotomous outcome data, school clustering, levels of strategy implementation, and student or school characteristics that are potential confounding variables. Usual assumptions of linear regression will be tested (including linearity, independence, constant variance and normality), with variations from normality adjusted for using the robust variance estimator. For all outcome analyses, school will be included in the model as the clustering unit.

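### Resilience is to be judged by comparing medians, but the only test named is a linear GEE of means, and the two can disagree

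*Protocol article*

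**What the plan says.** In the protocol article, the Statistical analysis subsection on secondary resilience outcomes has two sentences.

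- The first gives a reason, "Assuming resilience scores are not normally distributed (as with the data from the pilot study", and then the rule: "comparison of median scores will be made post-test between Grade 10 students in intervention and control schools to determine intervention effectiveness".
- The second names the model: "Linear regression models (GEE) will test differences in overall sub-scale levels of resilience factors (predictor variable being treatment group".

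Two statements in the subsection on primary outcomes bear on this. Non-normality is handled there, "with variations from normality adjusted for using the robust variance estimator", and clustering is covered generally: "For all outcome analyses, school will be included in the model as the clustering unit".

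The section on secondary outcome measures lists 14 subscales of 2 to 6 Likert items each, the shortest being "cooperation and communication (2 items". It gives neither the number of response options nor the scoring rule.

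**The concern.** A linear GEE with treatment group as predictor estimates the difference in mean score between arms. The preceding sentence assigns the decision on effectiveness to the medians. No test, interval or model is attached to the median comparison, and no sentence ranks the two. Read literally, the plan decides on one quantity and tests another.

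The reason given does not resolve this. If non-normality ruled out means, it would count equally against the linear model in the next sentence. If a robust variance deals with it, medians are not needed.

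At stake is how each resilience score is read. A subscale could show a significant mean difference beside identical medians, or different medians with no significant mean difference. Over 14 subscales, that leaves room to choose the reading after the data are seen.

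**Working it through.** **1. The plan's own figure.** No detectable difference is stated for resilience, so the smoking figure serves as a check on the inputs in the Sample size section (1,020 control and 1,700 intervention students in Grade 10, 12 and 20 schools, ICC 0.01).

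- Students per school: 1,020/12 = 85 and 1,700/20 = 85.
- Design effect: 1 + (85 − 1) × 0.01 = 1.84.
- Effective numbers: 1,020/1.84 = 554 and 1,700/1.84 = 924.
- Power for 14.0% against 9.2%, taken as two-sided 5% (sidedness is not stated): 80.5%. This agrees with the stated 80% for a difference of 4.8 points.

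**2. What the mean difference can detect.** Assuming the same ICC applies to resilience, the detectable standardised difference is 2.80 × √(1/554 + 1/924) = 2.80 × 0.0537 = about 0.15 SD at 80% power. The model already named is therefore sensitive to small effects.

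**3. How finely a subscale median can move.** Assume a subscale score is the mean of k items with K options. It takes k(K − 1) + 1 values in steps of 1/k.

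- 2 items, 4 options: 7 values, step 0.5.
- 6 items, 5 options: 25 values, step 0.17.

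**4. Population medians against means.** Sixteen assumed scenarios were simulated: 2, 3, 4 or 6 items; 4 or 5 options; skewed or near-symmetric responses; latent inter-item correlation 0.5.

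| Latent shift | Mean difference (SD) | Median unmoved | Median moved |
|---|---|---|---|
| 0.1 | 0.07–0.09 | 12 of 16 | 4 of 16 |
| 0.2 | 0.14–0.18 | 9 of 16 | 7 of 16 |
| 0.3 | 0.21–0.27 | 5 of 16 | 11 of 16 |
| 0.5 | 0.33–0.45 | 1 of 16 | 15 of 16 |

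At shift 0.2, every median that moved did so by one full step (0.17 to 0.5 points). Two scenarios show the extremes:

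- Two skewed 4-option items: a mean difference of 0.33 SD (0.33 × 0.69 = 0.23 points) left the median unchanged.
- Three skewed 4-option items: a mean difference of 0.078 SD (0.078 × 0.64 = 0.05 points) moved the median by 0.33 points.

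**5. Simulated trials.** For 12 scenarios, 300 trials each were run with 20 against 12 schools, 85 students per school and ICC 0.01. A t-test on school means stood in for the linear GEE.

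- Latent shift 0.2: the mean test had 86–94% power. The two arm medians were identical in 1% to 100% of trials, depending on scenario, and in more than 60% of trials in 5 of the 12.
- No effect: the arm medians still differed in 0% to 48% of trials.

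**6. The reason for medians.** The analysis has 1,020 + 1,700 = 2,720 students, about 85 per school. Means of that many bounded scores are close to normal whatever the shape of the individual scores, and a robust variance is already in the plan. Non-normality alone therefore does not call for medians.

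**The case against.** The strongest reply is that the plan has one inferential test, the linear GEE, and that the medians merely describe the scores. Only the second sentence speaks of testing. That may well be the intent, but the first sentence ties effectiveness to the medians, so the wording needs changing even on this reading.

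A second reply is that the medians may be of the overall internal and external scores, which the Background reports for the pilot, and not of the subscales. Those have 2 + 4 + 3 + 3 + 3 + 3 = 18 and 6 + 3 + 6 + 3 + 6 + 3 + 3 + 3 = 33 items, so the argument about coarse steps would not apply to them. This stands as a limit on that argument, because the article does not say which scores are meant. The mismatch remains: the aggregate scores would then have a deciding comparison with no named test.

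Two stronger readings are tempting, and the documents support neither.

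- A reader might infer that the medians will be compared by a test that ignores schools, with too many false positives. No such test is named, and the statement "For all outcome analyses, school will be included in the model as the clustering unit" covers resilience too.
- A reader might infer that a median on short scales can hardly register an effect at all. In the scenarios above it moved in 7 of 16 at shift 0.2 and 15 of 16 at 0.5. It is coarse and erratic rather than insensitive throughout.

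Finally, covariates are often left to an analysis plan. That is fair: adjustment is offered as an improvement on a model whose only stated predictor is treatment group, not as the correction of an error.

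**Conclusion.** The point holds as an inconsistency in the stated text: medians are said to decide effectiveness on resilience, and means are tested. The two can disagree at effect sizes that the named model would usually detect. How often they would do so cannot be fixed from the article. The figures rest on assumed response options, score distributions, inter-item correlation and item-mean scoring, on ICC 0.01 applying to resilience, and on the medians being of subscales. The mismatch itself needs none of these assumptions. It is confined to a secondary outcome and leaves the primary substance-use analysis and the sample size untouched. It is worth correcting because the correction is cheap and removes a choice that could otherwise be made after seeing the data.

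**What to change.** In the subsection on secondary resilience outcomes:

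- State which scores are analysed. For each, make the GEE mean difference between arms with its 95% CI, clustered by school, the single basis for judging effectiveness.
- Adjust that model for the Grade 7 score, which is already collected, and for the two stratification factors (engagement in the national initiative and school size).
- Report medians and quartiles descriptively only, and remove the clause that ties effectiveness to them.

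The cost is a change of wording, slightly more analysis and a stated way of handling students with a missing Grade 7 score. The linear GEE is already planned and no new data are needed.

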#### School environment survey outcomes

Existing resilience intervention implementation collected via the school environment surveys in both intervention and control groups will be compared at both baseline and follow up using descriptive statistics.

#### Implementation cost

Costs will be calculated with the support of a health economist from the perspective of routine school delivery (development and research costs will be excluded). The proposed costing approach has previously been successfully undertaken and reported by the study team [59,60].

## Discussion

To the authors’ knowledge this is the first randomised controlled trial to evaluate the effectiveness of a comprehensive school-based resilience intervention, inclusive of explicit adoption strategies, in decreasing the self-reported tobacco, alcohol and illicit drug use of adolescents attending disadvantaged secondary schools. The intervention has been found to be feasible and acceptable when piloted in three secondary schools.

The current study offers the opportunity to provide evidence that a resilience approach is effective in addressing adolescent substance use in line with the recent reviews that suggest this. If the results indicate the resilience intervention is effective in decreasing the prevalence of adolescent substance use, a new and strengthened intervention model will be available to aid policy makers and educationalists in implementing interventions targeting adolescent substance use, inclusive of program adoption strategies.
